## Methods

### Study design and setting

This pragmatic cluster randomised trial design involves 60 ECEC services in Perth metropolitan and Peel regions of Western Australia. The design was selected to maximise the applicability to ECEC services, that is, to test the Play Active physical activity policy intervention and accompanying implementation support strategies with a wide range of ECEC staff (directors and educators), while simultaneously enabling the program to be as close to real world conditions as possible [26]. At the conclusion of baseline data collection, ECEC services will be randomly allocated to either the intervention (physical activity policy template plus six implementation support strategies) or wait-listed comparison groups. Primary and secondary trial outcomes will be assessed for change immediately following the (up to 6 month) intervention period. The trial is registered through the Australian New Zealand Clinical Trials Registry (reference number 12620001206910, registered 13/11/2020). An overview of the study design, schedule for enrolment and study assessments is shown in Table 1.

**Table 1 Tab1:**
[figure not shown]
Schedule of enrolment, intervention, and assessments for the evaluation of the Play Active policy intervention and implementation support

Primary outcomes: educator-reported frequency and amount of time per day provided for children’s physical activity, sedentary and screen time. Secondary outcomes: educator physical activity practices, self-efficacy, motivation, attitudes and beliefs, social support, supportive physical environment and professional development training. ^1^For services allocated to intervention group only

The setting for this pragmatic trial are ECEC long-day care services, which provide centre-based childcare by professional staff for large groups of young children prior to formal compulsory schooling [27]. In Australia, ECEC long-day care services are mostly privately owned by providers, with the vast majority of providers approved to operate a single service only (81%), requiring enrolment and a daily fee for service [28]. ECEC services are highly regulated; the Australian National Quality Framework for ECEC outlines minimum standards across seven quality areas, including quality area 2.1.3 which states ‘healthy eating and physical activity are promoted and appropriate for each child’ [15]. As of February 2021, the regulating body, the Australian Children’s Education and Care Quality Authority reported there were 557 ECEC long-day care services located in the Perth and Peel metropolitan region of Western Australia. As the National Quality Framework also sets out minimum educator to child ratio requirements for ECEC services, there was an average of 66 approved places for children per service in the study region (range = 13–223 children).

### Eligibility criteria

Long-day ECEC services located in Perth and Peel, Western Australia will be eligible to participate. Ineligibility criteria include: long-day ECEC services catering exclusively for children requiring specialist care, mobile preschools, and Department of Education and Communities preschools; ECEC services already involved in an alternative randomised controlled trials currently underway in Perth, Western Australia; and ECEC services that have had a significant change in management within the last 3 months or expect a change in management in the next 3 months. Within each ECEC service, all permanent part- and full-time staff educators will be eligible to participate in the trial. Casually employed educators will be excluded. Within each ECEC service, all attending children aged 1–5 years who have not yet commenced formal schooling (pre-primary) will be eligible for participation in the study with parental consent. Exclusion criteria for attending children are a recognised disability (physical, emotional/behavioural or intellectual) that would affect participation in physical activity, and attendance of full-time formal schooling which would prohibit whole days spent in ECEC.

### Participant recruitment and consent

To closely align with real-world dissemination strategies, ECEC services will be recruited via an ‘Expression of Interest’ form available on one of the study partner’s (Cancer Council Western Australia) website. A launch event was used to publicise the new Play Active program and inform services how to express their interest in receiving the physical activity policy template and implementation support strategies. ECEC services who express interest will be contacted by the research team using a combination of modes (e.g., email, telephone) to invite them to take part in the pragmatic trial. ECEC providers with multiple services will be contacted and all services invited to participate. Recruitment commenced January 2021 and is ongoing. Eligible service directors will be provided with study information and asked to provide consent for their service to participate in the trial. Directors will then be asked to provide contact details for their eligible educators so that the research team can invite them to participate (consent process included as part of the educator survey). Directors will also be provided with parent information packs to distribute to their families and consent forms for children’s data from the educator completed brief energetic play assessment tool to be provided to the research team.

### Sample size and power

Based on a 15 min per day change in the primary outcome variable (i.e., average change in educator reported time allocated for children to be physically active indoors and outdoors), this trial will require a total of 60 services with 108 educators per group (80% power, 2-tailed alpha level of 0.05) to detect a moderate effect size of 0.4. After adjusting for clustering of educators within services, an educator ICC of 0.01–0.05 and a 30% dropout at follow-up data collection, 309 educators (6 per service) from 60 services will be recruited. This represents 11% of long-day care services in the Perth, Western Australia region.

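### The sample-size paragraph gives a recruitment total (309) that does not match its own 6 per service in 60 services (360), and the step it describes as adjusting for clustering adds only dropout

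*Protocol article*

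**What the plan says.** All the figures are in one paragraph of the protocol article, Methods, Sample size and power. The target is a 15-minute daily change, expressed as an effect size: "to detect a moderate effect size of 0.4", with "80% power, 2-tailed alpha level of 0.05". The first size statement is that "this trial will require a total of 60 services with 108 educators per group". The next sentence moves to recruitment. It opens "After adjusting for clustering of educators within services, an educator ICC of 0.01–0.05 and a 30% dropout" and ends "309 educators (6 per service) from 60 services will be recruited". The paragraph does not give the design effect, the cluster size used in it, which ICC in the range was used, or whether 108 is before or after clustering.

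**The concern.** Two things do not fit. First, the final clause gives a total, a number per service and a number of services, and the product of the last two is not the first. Second, the order of the sentences tells the reader that 108 per group was enlarged for clustering and then for dropout to reach 309, but dropout alone accounts for the whole increase.

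The recruitment target and the power claim both rest on this paragraph, and Participant recruitment and consent describes recruitment as ongoing. Which total is meant decides whether the 80% statement holds over the whole ICC range that the plan gives. A reader also cannot tell what allowance for clustering was made.

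**Working it through.** **Inputs, all from Sample size and power:** effect size 0.4; two-sided alpha 0.05; power 80%; 108 educators per group; 60 services; ICC 0.01–0.05; dropout 30%; 309 recruited; 6 per service. Assumed here: 30 services per group and equal cluster sizes.

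**1. The plan's own total.** 2 × 108 = 216, and 216/(1 − 0.30) = 308.6, which rounds up to 309. The figure is reproduced with dropout alone.

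**2. Total against number per service.** 6 × 60 = 360. In reverse, 309/60 = 5.15 per service and 309/6 = 51.5 services. The gap is 360 − 309 = 51 educators, or 16.5% of 309.

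**3. Is clustering inside 108?** Without clustering, n per group = 2(1.960 + 0.842)²/0.4² = 98.1 by normal approximation, or 99.1 (so 100) by t test. The ratio of 108 to this is 108/98.1 = 1.10 or 108/100 = 1.08. Take the design effect as 1 + (m − 1) × ICC and solve for the ICC:

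- m = 216/60 = 3.6 completers per service: 0.08/2.6 = 0.03 to 0.10/2.6 = 0.04.
- m = 6: 0.10/5 = 0.02 (starting from 98.1).

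Each value lies inside the stated 0.01–0.05. So 108 is compatible with a clustering allowance already made, at an ICC below the top of the range.

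**4. Power under each total.** Effective n per group = completers per group / design effect. Power comes from the standardised difference 0.4 × √(effective n/2), by normal approximation and by noncentral t with 58 df (60 services − 2).

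| Recruited | Completers (70%) | Per service | ICC | Design effect | Effective n per group | Power, normal | Power, t 58 df |
|---|---|---|---|---|---|---|---|
| 309 | 216 | 3.6 | 0.01 | 1.026 | 105.3 | 82.7% | 81.4% |
| 309 | 216 | 3.6 | 0.05 | 1.130 | 95.6 | 79.0% | 77.6% |
| 360 | 252 | 4.2 | 0.01 | 1.032 | 122.1 | 87.8% | 86.7% |
| 360 | 252 | 4.2 | 0.05 | 1.160 | 108.6 | 83.8% | 82.6% |

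With 309 recruited, power by normal approximation is 79.9% at ICC 0.04, so it crosses 80% at about that value. By t with 58 df it crosses between ICC 0.02 (80.5%) and 0.03 (79.5%).

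**The case against.** The best defence is that the calculation is sound and only badly told. 98.1 × 1.10 = 107.9, so 108, where 1.10 is the design effect for 6 per service at ICC 0.02; then 216/0.70 gives 309. On completers, 100 × (1 + 2.6 × 0.03) = 107.8 also gives 108. The plan does not say that it was sized at an ICC of 0.05, so choosing a value inside the range is a judgement and not an arithmetic error. The 6 may be 5.15 rounded up to whole educators. All permanent educators are eligible and no quota per service is stated, so the mismatch need not change who is approached. The 58-df test is stricter than the normal approximation, and the degrees of freedom for the planned mixed model belong to an analysis plan that is not shown.

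Most of this stands, and it limits the point. It does not make 309, 6 and 60 agree, and it does not match the order of steps that the text gives. Nor does the text identify a route: 216 × 1.10 × 1.3 = 308.9 also reaches 309, by a different dropout formula and with clustering applied after 108.

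A reader might infer three stronger things that the document does not support:

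- *No clustering inflation at all.* 108 exceeds the unclustered 98–100 per group, so an allowance may already be there.
- *A need for 349 to 386 recruits.* These come from 216 × 1.13/0.70 and 216 × 1.25/0.70, which treat 108 as the unclustered requirement. It is larger than that requirement. The upper figure also takes 6 analysed per service, where 216 completers average 3.6.
- *Power of 75% from unequal services.* This needs an assumed coefficient of variation of 0.65. The 13–223 range under Study design and setting counts approved child places across the region, not participating educators per service.

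**Conclusion.** The paragraph is wrong as written on two counts. The 309 total contradicts 6 per service in 60 services, which is 360. The step said to adjust for clustering adds only dropout to 108 per group. The first count needs no assumption. The second concerns the description: clustering may well be inside 108.

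The consequence for power is modest. If 309 is the target, power falls 1.0 point (normal) or 2.4 points (t, 58 df) short of 80% at ICC 0.05 and is above 80% at ICC 0.01. If 360 is the target, 80% is met over the whole stated range. These figures assume equal cluster sizes and 30 services per group. Unequal sizes, or services of one provider allocated together as the Randomisation section allows, would tend to lower power by an amount that the document does not allow to be computed. This is a correction worth making because it costs nothing; it is not a defect that threatens the design.

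**What to change.** Restate the paragraph with one consistent set of figures, as one of:

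- 309 educators recruited, about 5 per service, 216 analysed, power about 78–83% over ICC 0.01–0.05; or
- if 6 per service is the operational target, 360 recruited, 252 analysed, power about 83–88% over the same range.

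In either case, say whether 108 per group already includes clustering, give the ICC, cluster size and design effect used, and show the clustering step separately from the dropout step. If 309 is kept, the cost is wording and a slightly less favourable power statement at the upper ICCs. If 6 per service was already the working target, 360 only records it. Neither version adds services or recruitment beyond what the plan already states.

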### Randomisation

Services will be randomised to the intervention or wait-listed comparison group after baseline data collection. Using a central randomisation procedure, the randomisation sequence will be generated using a computerised random number function in Microsoft Excel. Due to the increased chances of contamination between services of the same provider if allocated to different groups, these services will be randomly allocated to the same group or two different groups grouped by geographical location. The research team member generating the allocation sequence and assigning services to their group will not be involved with recruitment, data collection or intervention delivery. Due to the nature of the intervention (i.e., implementation of a policy), it is impossible to blind services to their group allocation, thus this will be an open trial without masking and services will be aware of the group they are assigned to.

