### Statistical analysis

Analysis will be undertaken following intention-to-treat principles. To examine the representativeness of the study sample, service-level characteristics will be compared with the full sampling frame of Perth and Peel ECEC services at the time of recruitment using data available from Australian Children’s Education and Care Quality Authority [28]. The primary outcome variables of educator-reported frequency and time provided for children to be physically active will be analysed using generalised linear mixed effects models and will include fixed effects for socio-demographics, time, intervention, time-by-intervention interaction, and random effects for individual educators nested within services. Factor analysis and latent class analysis will be considered for secondary outcome items prior to being similarly analysed using generalised linear mixed effects models. Open-ended, qualitative data responses to process outcome items in the post-intervention director and educator surveys will be thematically analysed according to a prepared coding framework and consensus reached by at least two research team members not involved with data collection. For any discrepancies, a third team member will make the final decision. Other process evaluation data will be summarised descriptively. All quantitative data preparation and analyses will be carried out using SAS 9.4 or above and Stata 17 or above, and qualitative analysis using NVivo 20.0 or above.

As part of dissemination, a study report presenting the overall findings of the research will be prepared for all participants and stakeholders. Peer-reviewed publications and presentations will allow the results to be disseminated to the scientific community. Results will be reported according to Consolidated Standard of Reporting Trials guidelines [26].

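### Multi-service providers are allocated in blocks, but the sample size and primary model stop at the service; where blocks stay in one arm this can make the intervention standard error too small and the stated power too high

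*Protocol article*

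**What the plan says.** All references are to the protocol article.

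- **Randomisation, general rule:** "Services will be randomised to the intervention or wait-listed comparison group after baseline data collection".
- **Randomisation, exception:** because of possible contamination between services of one provider, "these services will be randomly allocated to the same group or two different groups grouped by geographical location".
- **Participant recruitment and consent:** "ECEC providers with multiple services will be contacted and all services invited to participate". Blocks of services are therefore expected, and complete ones are sought.
- **Sample size and power:** 108 educators per group from 60 services, 80% power, two-sided 5% level, "to detect a moderate effect size of 0.4". The inflation is described as "After adjusting for clustering of educators within services", with an educator ICC of 0.01 to 0.05 and 30% dropout, giving 309 educators.
- **Statistical analysis:** a generalised linear mixed model with time, intervention and their interaction, and "random effects for individual educators nested within services".
- **Study design and setting (text after Table 1):** 81% of Australian providers run a single service.

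No level above the service appears in the sample size or the model.

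**The concern.** The allocation rule creates a cluster level that the inference does not contain. Services of one provider are treated as linked when allocated and as independent when analysed. If their changes from baseline tend to move together and they sit in the same arm, the trial holds fewer independent units than 60. A model that stops at the service then gives a confidence interval that is too narrow for the time-by-intervention effect, a type I error above 5%, and less power than stated.

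The random effects and the level of the sample-size adjustment are both stated in the article, so this is a mismatch within the text and not a detail left to a fuller document.

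**Working it through.** **1. The plan's own figures.** For an effect size of 0.4, n per group = 2(1.96 + 0.84)²/0.4² = 98.1, so 99. Completers per service: m = 216/60 = 3.6. The service-level design effect 1 + (m - 1)ICC gives 101 per group at ICC 0.01, 106 at 0.03 and 111 at 0.05. The stated 108 lies inside this range, and 216/0.70 = 309 is exact. The figures reproduce with service clustering alone, so there is no sign of an allowance for providers.

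**2. How many services might be in blocks.** The 81% is a share of providers, not of services. If the other 19% run two services each, the share of services in multi-service providers is 0.38/(0.81 + 0.38) = 32%. With five each it is 0.95/(0.81 + 0.95) = 54%. This assumes that the trial resembles the national figure.

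**3. Design effect with a provider level (providers kept whole).** DE = 1 + (m - 1)ICC_s + m(K - 1)ICC_p. Here ICC_s is the correlation within a service, ICC_p the correlation between services of one provider, and K = Σk²/Σk over providers of k services. These are correlations of change.

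Assumed mix: 30 single services, 4 providers of 3 and 3 of 6. That is 60 services in 37 units, of which 30/37 = 81% are single, matching the cited share. K = (30 + 36 + 108)/60 = 2.9, so DE = 1 + 2.6 ICC_s + 6.84 ICC_p. Power uses 108/DE per arm and t with 37 - 2 = 35 df. Type I error is for a t test on service mean changes, from simulation of several thousand null trials per setting (Monte Carlo error about 0.4 points).

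| ICC_s | ICC_p | DE | 108/DE | Power | Type I error |
|---|---|---|---|---|---|
| 0.01 | 0.005 | 1.060 | 101.9 | 79% | 5.1% |
| 0.05 | 0.01 | 1.198 | 90.1 | 74% | 5.6% |
| 0.05 | 0.025 | 1.301 | 83.0 | 71% | 6.4% |
| 0.05 | 0.05 | 1.472 | 73.4 | 65% | 7.4% |

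With service clustering only (t, 58 df), power is 81% at ICC_s 0.01 and 78% at 0.05.

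**4. Worst case.** With 10 single services and 5 providers of 10 (15 units), K = (10 + 500)/60 = 8.5. At both ICCs 0.05, DE = 1 + 0.13 + 3.6 × 7.5 × 0.05 = 2.48 and 108/DE = 43.5. Power is 41% and type I error about 15%.

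**5. The named model itself.** The model-based standard error of the time-by-intervention term was compared with its true value for 60 services, 5 educators each and 70% followed up, with every service in a provider of k services. Variances are fractions of a total of 1.

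- Provider variance constant over time (0.05): ratio of true to model standard error 1.00, because it cancels from the change.
- Provider-by-time variance 0.01 to 0.02, providers kept whole: ratio 1.07 to 1.14 for k = 2 and 1.34 to 1.61 for k = 10 (actual type I error about 6.7% to 22%).
- The same variance, each provider divided evenly between arms: ratio 0.98 to 0.99.

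In this set-up 0.01 to 0.02 corresponds to a correlation of change of 0.01/0.47 = 0.021 to 0.02/0.47 = 0.043. Part of the inflation would arise even for single services, since the service effect in the working model is constant over time: roughly √(1 + 2.5 × 0.021) = 1.03 to √(1 + 2.5 × 0.043) = 1.05, with 3.5 completers per service.

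**The case against.** The strongest reply has three parts.

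**The rule has two branches.** A reader might infer that providers always go whole to one arm and that standard errors are therefore too small. The text also allows a provider to be divided by location between the two groups. In the mix of step 3 with every provider divided evenly, simulated type I error was 4.4% at ICC 0.05, slightly conservative. This stands: the direction of the error depends on how many providers are divided, which is not stated. It does not remove the problem, because the article gives no rule for choosing between the branches, and a location block is still allocated as one unit.

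**The stated reason is contamination, not similarity.** A reader might infer that the plan itself says services of one provider share management and policies. It does not. Contamination is leakage between arms. Each service also has its own director, gives its own consent and personalises its own policy. This stands too: correlated change within a provider is plausible, but it is an assumption.

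**The large figures need extreme inputs.** The 15% error and 41% power put 50 of 60 services in five providers, with a provider ICC equal to the top of the range that the article gives for services. With few or small providers and a low ICC the effect is negligible: if a quarter of services sit in providers of two (service ICC 0.05, provider ICC 0.01 to 0.05), power by the normal approximation is 78.6% to 77.4% against 79.0%. The type I errors in step 3 also come from a test on service means, not from the named model.

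These points limit the size and the certainty. They do not reconcile the allocation rule with the sample size and the model.

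**Conclusion.** The mismatch holds as a conditional point. Multi-service providers are allocated as blocks, and neither the sample size nor the primary model has a level for them. Harm requires blocks kept in one arm and positive correlation of change over time between their services. A provider effect constant over time does no harm to the time-by-intervention term, and even division between arms leaves its standard error about right or slightly too large.

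For the mix that matches the cited 81%, with all providers kept whole and a provider ICC of 0.005 to 0.05, type I error is about 5-7%. Power is about 79% down to 65%, against 81% to 78% with service clustering only. The figures of 15% and 41% are a worst case, not an expectation. The mix, the share divided and the provider ICC are all assumptions. The point should be fixed because the primary confidence interval depends on it, but the documents do not show that the analysis would be anti-conservative.

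**What to change.** - **Statistical analysis:** define the allocation unit as it was used (single service, whole provider, or provider-by-location block). Make it the top cluster level for the time-by-intervention contrast, through a unit-by-time random effect or cluster-robust inference at that level. In either case use a small-sample correction based on the number of units. A provider random intercept alone is not enough, because it does not correct this standard error.
- **Randomisation and reporting:** report the number and size of allocation units per arm, and which providers were divided.
- **Sample size and power:** restate power as a range under stated provider-level ICCs and an expected provider mix.

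The cost is small. The allocator must already hold the provider and block identifiers, so no new data are needed. The price is somewhat wider confidence intervals and a slightly less favourable stated power.
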